### Interventions

The MBDCP was formulated by the principal investigator and his team (which includes a qualified MBCT therapist, clinical psychologist, nurses specialized in dementia care, social workers, and a psychiatrist) by modifying the prior MBCT protocol that was tested and adopted in our pilot and main study [22, 25]. The MBDCP includes 6 weekly 90-min group-based sessions delivered through a face-to-face (1st, 2nd, and 6th sessions) and online approach (3rd, 4th, and 5th sessions), as shown in Table 1. The online session is designed for self-directed learning. The caregivers will watch a teaching video (e.g., a video demonstrating mindfulness practices) through a website. The MBDCP includes different mindfulness practices (e.g. body scanning, mindful walking and mindful eating), psychoeducation on caregiving, and group sharing. The program aimed to enhance participants’ mindfulness skills through formal and informal mindfulness practice and help them to integrate these skills into their everyday life. Six sessions are adopted because in our prior studies showed that most caregivers were able to learn the mindfulness skills in the first four sessions, and two more sessions (5^th^ & 6^th^) were delivered to help the caregivers develop an action plan for further continuous practice. The duration of the intervention is shortened from 120 to 90 min because the in-class revision of practice will transform to online self-directed practice, in which all teaching materials and an audio recording of guided mindfulness activities will be provided to the participants through the website to enhance their daily practice and self-learning.

**Table 1 Tab1:** Contents of the mindfulness-based Dementia Caregiving Program

Week	Teaching mode	Main theme	Contents (90 min per session)	Home practice
1	Face-to-Face	Caregiving stress and automatic pilot	Establishing the orientation of the class The raisin exercise (eating meditation) 13-min body scan Reaction to stress	45-min body scan for 6 out of 7 days Mindfulness of a routine practice
2	Face-to-Face	Thoughts and feelings	Exercises on thoughts and feelings related to dementia caregiving Mindful stretching and breath meditation Mindful movements 3-min breathing space	10 min of mindful breathing for 6 out of 7 days Pleasant experience calendar (one example daily) Mindfulness of a routine practice
3	Online	Facing difficulty with mindfulness	Exercises focusing on unpleasant caregiving experiences Practising seeing and hearing Sitting meditation (awareness of breath and body, and of responses to painful sensations)	40 min of mindful movements or stretching and breathing meditation for 6 out of 7 days Unpleasant experience calendar (a different experience for each day) 3-min breathing space, 3 times daily
4	Online	Mindful communication and responses	Practising seeing and hearing Mindful communication with people with dementia 3-min breathing space Responding to the behaviour of the care-recipient	Sitting meditation, 6 out of 7 days 3-min breathing space (3 times a day) 3-min breathing space – responsive (whenever one notices unpleasant feelings)
5	Online	Thoughts are not facts	Sitting meditation Exercises on thoughts and alternative viewpoints 3-min breathing space (responsive) Identifying habitual emotional reactions to difficulties resulting from caregiving	Select a guided meditation to practise at least 40 min per day 3-min breathing space (3 times a day) 3-min breathing space – added instructions (whenever one notices unpleasant feelings)
6	Face-to-Face	Taking care of yourself	Sitting meditation with breath, body, sounds Exploring difficulties in mindfulness Exercise on looking forward and preparing for the future	3-min breathing space (3 times a day) Select from all different forms of practice and apply them on a regular basis Develop actions to be used in the face of low moods

All of the contents in the Mindfulness-based Dementia Caregiving Program (MBDCP) will be closely related to dementia caregiving (e.g., instructions on how to respond mindfully to the behaviour of the care-recipient, exercises focusing on unpleasant experiences resulting from caregiving). Weekly online follow-up sessions provided by the facilitators via the website will be conducted to monitor the caregivers’ progress in learning and practising mindfulness. Drawing on the experience from our pilot study, the group size of the MBDCP group will be 15 to 18 participants to ensure adequate interactions between the mindfulness facilitator and all the caregivers. The caregivers can also communicate and share their practice experience with classmates via the online platform, as group discussion and mutual support is regarded as an active component of the MBI. All teaching materials, including the online video, will be prepared by a qualified MBI therapist. The qualified MBI therapist will mainly train the facilitators on how to deliver the three face-to-face training sessions. Drawing from a prior study on designing a Mindfulness Ambassador Programme [31], the facilitator will undergo a 21-h training (3 days) session to learn how to deliver mindfulness skills and how to answer the participants' questions. After the training session, the facilitator must pass a practical assessment by delivering two sessions of MBDCP to two groups of caregivers in the presence of a qualified MBI therapist, before being allowed to run the MBDCP. The criteria for the inclusion of the facilitator will be (1) aged 18 or above, (2) with at least 1 year of working experience in the field of social welfare, health care, or education (for better social and communication skills).

### Intervention fidelity control

All face-to-face sessions will be audio-recorded to check for fidelity to the intervention. After each session, an independent researcher with prior training in mindfulness will listen to the audio recording and monitor the intervention’s fidelity using a pre-designed fidelity checklist. This is to ensure that all the MBDCP sessions will be executed by the facilitator as intended. Based on the recommendations of the NIH Behavior Change Consortium [32], a fidelity rate of > 90% will be considered as acceptable. For online teaching, the website will guide the participants to watch each online video one by one. They will not be allowed to skip any sessions.

### Control group (Education on dementia care)

The family caregivers in the control group will receive brief education on dementia care which consists of 6 weekly 90-min group sessions, which will be delivered through a face-to-face (1st, 2nd, and 6th sessions) and online approach (3rd, 4th, and 5th sessions), with the same duration frequency and group size as the sessions in the MBDCP. The contents of the education offered to the control group will include brief education sessions on dementia care, caregiving skills, and group sharing. The group will be led by a registered nurse with experience in dementia care or elderly care.

### Instruments and measures

Data in this study will be collected via face-to-face data collection. The socio-demographic data will be collected at baseline (T0), while the outcome measurements will be collected at T0, immediately after the intervention (T1), and at the 6-month follow-up (T2). An independent assessor who is blinded to the group assignment (i.e. a research assistant with relevant experience and training) will carry out all these face-to-face assessments. Please find below the details of the outcome measurements:

### Primary outcomes measurement

#### Caregiving stress

Perceived caregiving stress will be assessed by the Chinese version of Perceived Stress Scale (PSS-10) [33]. It contains 10 items which measures the extent to which an individual has appraised their life as stressful. Respondents will be asked how often they felt in a certain way on a 5-point Likert scale from 0 to 4 (from never to very often). The total score ranged from 0 to 40, with a higher score indicating a higher perceived level of stress. The PSS-10 demonstrated satisfactory psychometric properties in the Chinese clinical samples [34].

### Secondary outcome measurements

#### Depression

Depressive symptoms will be assessed by the Chinese version of the Center for Epidemiologic Studies Depression Scale (CESD) [35]. It is a 10-item measure that asks respondents to rate how often they experience symptoms of depression (e.g. poor appetite, loneliness) over the past week. Respondents will be asked to indicate their response with a 5-point Likert scale from 1 (never) to 5 (very often). The total score ranges from 0 to 30, with a higher score representing more depressive symptoms. The CESD demonstrates satisfactory validity and reliability on the Chinese adults attending primary care services [36].

### Positive aspect of caregiving

Positive caregiving experience will be assessed by the Chinese version of the Positive Aspect of Caregiving Scale (PAC) [37]. The PAC is an 11-item instrument that measures the degree to which providing care to their relative with dementia has enabled them ‘feel important’ and ‘feel appreciated’. They will answer the questions on a 5-point Likert scale. The total score ranged from 11 to 55, with higher score indicating a more positive perception of caregiving. The PAC is a valid and reliable measurement among Hong Kong Chinese caregivers [38].

### Caregiving burden

Caregiving burdens will be assessed by the Chinese version of Zarit Burden Interview (ZBI) [39]. The scale comprises of 22 items which assess the subjective burden of caregivers. Respondents will be asked to rate their extent to which caregivers perceived their emotional or physical health, social life, and financial status to have changed as a result of caring for their PWD. The response option will be presented in a 5-point Likert scale (0 = None, 4 = Extremely distressing). The total score ranges from 0 to 88, with a higher score representing a higher level of caregiving burden. The Chinese version of ZBI is a valid and reliable instrument to evaluate stress experienced by caregivers of PWD in Hong Kong [40].

### Dyadic relationship

The Dyadic relationship is assessed by the Chinese version of Dyadic Relationship Scale -caregiver version (DRS) [41]; It is an 11-item scale that measures negative and positive dyadic interactions from the perspective of caregivers. The scale includes a four-option response (from 1 strongly disagree to 4 strongly agree). The scale generates two subscale scores: dyadic strain (ranges from 5 to 20) and positive dyadic relationship (ranges from 6 to 24). A higher score on each of these scales indicates a higher level of strain and positive interactions respectively. The DRS demonstrates satisfactory validity and reliability among caregivers.

### Neuropsychiatric symptoms of patients and corresponding distress

The neuropsychiatric symptoms of the care-recipients will be assessed by the Chinese version of Neuropsychiatric Inventory through caregivers [42, 43]. NPI-Q is an informant-based instrument that measures the presence and severity of 12 symptoms in patients with dementia and caregivers’ distress. The caregivers will be asked to identify whether the symptoms of the care recipients had been present in the past week and rate the severity of the symptoms (from a Likert scale ranged from 1 to 3) and the corresponding distress to them (from Likert scale ranged from 1 to 5). The NPI-Q provides two scores, namely, total severity of symptoms (ranges from 12 to 36) and total distress scores (ranges from 12 to 60). The higher scores indicate a higher level of symptoms severity of care recipients and distress of caregivers respectively. The Chinese version of NPI-Q is a valid and reliable measurement among stroke patients in Hong Kong [43].

### Heart rate variability

Heart rate variability (HRV) will be measured as a biomarker by using validated Polar heart-rate monitors (Polar Vantage M, Polar Electro Oy, Finland) [44]. HRV will be interpreted following the Guidelines for the Standard Measurement and Interpretation of HRV (European Society of Cardiology and the North American Society of Pacing and Electrophysiology) using the frequency-domain method [45].

### Level of mindfulness

Participants’ level of mindfulness will be assessed and served as a process indicator of this study as our program aims to reduce caregivers’ stress by enhancing their mindfulness level. The Chinese version of Five Facet Mindfulness Questionnaire-Short Form (FFMQ-SF) will be used [46]; FFMQ-SF is a 20-item questionnaire that measures the five facets of mindfulness: observing, describing and acting with awareness, nonjudging of and nonreactivity of inner experience. Items are scored in a 5-point Likert scale (from 1-Never to 5-Very often). The total score ranges from 20 to 100, with a higher score indicating a higher level of mindfulness. FFMQ-SF demonstrates good validity and reliability in both non-clinical and clinical population of Hong Kong Chinese [47].

Furthermore, participants will be asked to record the frequency and duration of their mindfulness practice once a week via the online platform. They will also be asked whether they had complied with the practice regime in the past 7 days, using a score ranging from 0 (Not complied at all) to 10 (Fully complied).

### Socio-demographic data

This section includes the followings: 1. age, gender, marital status, and level of education, living status; 2. health-related information, including medical history, activity of daily living (ADL) and instrument activity of daily life (IADL), cognitive status, and medications; 3. Use of social and caregiving support such as respite care, daycare centers, and domestic helpers.

### Qualitative arm

Two rounds of semi-structured interviews with a group size of 4 to 5 will be conducted immediately after the intervention and at the 6-month follow up. The focus group aims to explore the participants’ perception and experience in attending the program in terms of the strengths, weaknesses, therapeutic components of the mindfulness intervention, and also the short-term (e.g. immediately after the intervention) and longer-term (e.g. 6-month after the intervention) impacts on their caregiving. A guiding question will be employed, which will open up new testimonies: “What is your experience in joining the mindfulness program?” The participants will be then asked about how the experience impact their caregiving in different stages, the elements that they find that is useful, and the skills, knowledge, and any other benefits that they gain in the program during and after the intervention.

### Study procedure

Participants will be recruited via convenience sampling. Potential participants will be referred to the research team from three community center which provides services to the PWD (Collaborators of the research team). An independent Research Assistant (RA) will screen for their eligibility to participate in this study. A written informed consent will be sought from all the participants after the study was explained and all questions were answered. Following this, the participants will be interviewed about their health-socio-demographic information and complete the baseline assessment. Upon completion of the baseline assessment, they will be randomly allocated into the intervention group and control group (described in random allocation).

Follow-up assessments will be conducted by an independent RA who is blinded to the group assessing immediately after the 6-week intervention (T1), and after the 6-month post-intervention (T2). Focus group interviews will be conducted by within one week after T1 and at the 6-month follow up (T2) by an independent senior research assistant who has received training in how to conduct semi-structured interviews. Each focus group will last for about 60 min.

To ensure the RA can act as an independent outcome assessor throughout the stud, he/she will receive prior training on all the outcome instruments and interview techniques. The RA training will be provided by the PI. It consists of role play and on-site assessment practice with different clinical vignettes. Prior to the start of the study and throughout the data collection period, the scores rated by the assessor and the RA will be compared. The inter/intra-rater reliabilities will be evaluated by intra-class correlations (ICC). An ICC > 0.9 will be considered as an acceptable level of reliability.

### Random allocation and allocation concealment

Permuted block randomization will be employed in this study following the allocation concealment mechanism. Using an online, computerized sequence generation randomization tool (www.randomizer.org), an independent RA will generate a list of the permuted block sequences of two group labels (1 = MBDCP group, 2 = control group) in a 1:1 ratio. The participants will receive notice of their group allocation in an opaque sealed envelope on the first day of the intervention. The group allocation lists will be concealed from the researcher, the staff of the elderly centres, and the outcome assessors.

### Ethical considerations

Ethical approval will be obtained from the Ethics Review Committee of The University and study venues, respectively. The research team will comply with all of the requirements of a study involving human subjects as stated in the Helsinki Declaration and subsequent updates and the Good Clinical Practice guideline. No adverse effects from practicing mindfulness were reported in our prior study. A data monitoring committee will be formed and the group will consist of four independent experts from the fields of mental health nursing, psychology and gerontology. Throughout the study period, the committee will receive updates on participants’ outcome data (e.g., level of anxiety, stress, and depression). They will be contacted/ referred to health care professionals for further assessments if needed.

### Data analysis

SPSS version 23.0 will be used to analyze the data. An intention-to-treat analysis will be adopted. The demographic data will be presented in the format of descriptive statistics. Normality assumptions for the variables will be checked using the Kolmogorov–Smirnov (KS) test. Independent sample T-test (two-tailed) or Chi-square test will be used to examine demographic and clinical profiles between the two study groups. Generalized estimating equations (GEE) will be used to examine the study outcomes between the intervention and control groups across the three time-points (T0, T1, and T2). The dependent variables will be the mean total scores of the psychological health outcomes in the GEE analysis. The group, time points, and group x time interaction will be the independent variables. The missing data will be estimated in the GEE model based on the maximum likelihood estimation. Since there were no known covariates in our previous study, this assessment of homogeneity will be to identify any potential covariance in the outcomes. The possible covariates, such as age, gender, level of education, compliance, and psychiatric comorbidity, will be entered as covariates in a secondary analysis. All data analyses will be conducted with two-tailed tests with a significance level of p < 0.05.

For the interview data, content analysis will be performed using QSR NVivo 11. All audio recordings of the interviews will be transcribed into Chinese by the RA and the transcriptions will be checked for accuracy by the PI. To ensure trustworthiness, the transcripts will be coded independently by two Cantonese-speaking researchers. They will then discuss the codes by grouping them into main and subcategories with the support of verbatim data. The subcategories will then be re-organized. A set of subcategories with supporting verbatim data will finally be generated to identify the major strengths and limitations of the interventions as well as the long-term and short-term impact on caregiving. Any disagreements between the two researchers will be resolved through discussion with the larger research team.

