### Sample size

The sample size is estimated based on the primary outcome of our study (perceived stress). This proposed study will adopt a simplified version of mindfulness training that differs from the protocol in our prior RCT [25]. Therefore, after considering the effect size of 0.36 in the prior meta-analysis on cognitive behavioural interventions for reducing stress in family caregivers of PWD [29], we adopted a conservative medium effect size of 0.40, which is similar to the effect size of psychological and behavioural interventions suggested by Cohen, to detect the mean difference in stress reduction between the intervention and control groups [30]. Considering the 20% attrition rate at 6 months that we found in our prior study, a sample size of 290 family caregivers (145 per group) is needed to achieve 80% power at 5% significance level (Two-sided). 20 caregivers from the intervention group will be purposively sampled to join in a focus group with a group size of 4 to 5 dyads per group one week after the intervention. After the intervention, equal proportions of participants with different levels (e.g., high, moderate, and low) of stress reduction will be selected.

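### The primary GEE leaves the arms free to differ at T0, so it estimates a difference in change; it is valid, but less precise than a model that adjusts for the pre-randomisation score

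*Protocol article*

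**What the plan says.** The Data analysis section applies GEE to the outcomes at T0, T1 and T2 and fixes the mean model: "The group, time points, and group x time interaction will be the independent variables". The baseline value of the outcome is not named as a covariate. The covariates that are named, "such as age, gender, level of education, compliance, and psychiatric comorbidity, will be entered as covariates in a secondary analysis", do not include it and do not enter the primary model. No working correlation is given.

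The Study procedure section sets the order of events: "Upon completion of the baseline assessment, they will be randomly allocated into the intervention group and control group".

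The Sample size section says "we adopted a conservative medium effect size of 0.40", in order "to detect the mean difference in stress reduction between the intervention and control groups". It allows for 20% attrition at 6 months and arrives at 145 caregivers per group. It gives no raw SD and no correlation between T0 and follow-up.

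**The concern.** With group, time and their interaction all in the model and T0 among the responses, the group main effect is the group difference at T0. The interaction at T1 or T2 is then the follow-up difference minus the T0 difference, which is the difference in mean change.

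Because T0 is measured before allocation, any group difference there is due to chance. The model estimates it anyway and subtracts it in full. A baseline-adjusted model subtracts only the fraction ρ that carries through to follow-up. The extra subtraction adds noise to the primary comparison that the collected data could remove. The Discussion expects recruitment of 290 caregivers to be difficult, so precision that needs no further participants has practical value.

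**Working it through.** **Inputs from the article.** Standardised effect 0.40; two-sided 5%; 80% power; 145 per group; 20% attrition at 6 months, so 145 × 0.8 = 116 completers per group.

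**Inputs assumed.** The correlation ρ between T0 and each follow-up score is taken as 0.3 to 0.7. Variances are equal over time, and clustering by intervention group is ignored. The working correlation is taken as exchangeable, with independence as a comparison.

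**The plan's own figure.** 2 × (1.960 + 0.842)² / 0.40² = 98.1, so 99 per group. Dividing by 0.8 gives 124 per group, or 248 in total (250 with a t-based calculation). The stated 290 does not follow from the stated inputs; it is larger. That is a separate matter. The steps below use 145 per group as stated.

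**What the interaction estimates.** In a check with complete simulated data, the free-T0 interaction equalled the difference in mean change to within rounding error (about 10⁻¹⁶), under both exchangeable and independence working correlations. With 20% missing at T2 it targets the same contrast but is no longer numerically identical to the completers' change-score difference.

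**Variance, complete data** (per person, in units of the raw-score variance)
- Change from T0: 2(1−ρ)
- Adjusted for T0: 1−ρ²
- Ratio: (1+ρ)/2, so the reduction is (1−ρ)/2

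| ρ (assumed) | Change | Adjusted | Reduction, complete data | Reduction at T2, 20% missing, exchangeable |
|---|---|---|---|---|
| 0.3 | 1.40 | 0.91 | 35% | 30% |
| 0.5 | 1.00 | 0.75 | 25% | 21% |
| 0.7 | 0.60 | 0.51 | 15% | 13% |

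The last column comes from the model-based variance of the three-time-point GEE. Constraining the T0 means to be equal and entering T0 as a covariate give the same values. At T1, where no loss was assumed, the reduction stays at 35%, 25% and 15%.

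**Power with 116 completers per group, 0.40 in raw-score SDs.** Power = Φ(0.40 × √(116/2) / √v − 1.96), where v is the variance above and 0.40 × √58 = 3.046.

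| ρ | Planned (change) | Adjusted |
|---|---|---|
| 0.3 | 3.046/√1.40 = 2.575, 73% | 3.046/√0.91 = 3.193, 89% |
| 0.4 | 3.046/√1.20 = 2.781, 79% | 3.046/√0.84 = 3.324, 91% |
| 0.5 | 3.046/√1.00 = 3.046, 86% | 3.046/√0.75 = 3.518, 94% |
| 0.7 | 3.046/√0.60 = 3.933, 98% | 3.046/√0.51 = 4.266, 99% |

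Planned power reaches 80% when √(2(1−ρ)) = 3.046/2.802 = 1.087, that is ρ = 0.41. Adjusted power is lowest at ρ = 0, where it is 86%. If dropouts' T0 and T1 scores are kept in an exchangeable GEE, the T2 figures at ρ = 0.3 are 76% against 89%, so the crossing point moves somewhat lower.

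**Power with 0.40 in change-score SDs.** Planned power is Φ(3.046 − 1.96) = 86% at any ρ. Adjusted power is 97%, 94% and 91% at ρ = 0.3, 0.5 and 0.7.

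**A common T0 mean under an independence working correlation.** The T0 scores then contribute nothing to the follow-up contrast, whose variance becomes 1. The ratio to the planned variance is 1/(2(1−ρ)): 0.71 at ρ = 0.3 (29% reduction), 1.00 at 0.5 (no gain), and 1.67 at 0.7 (67% increase).

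**The case against.** The planned model is not wrong. Under randomisation its interaction is an unbiased estimate of the difference in change, with a valid test. It also matches the quantity named in the Sample size section. Chance imbalance at T0 costs precision but does not bias the estimate over repeated randomisations. All of this stands, and it makes the point one of efficiency.

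A reader might infer that the planned analysis misses its stated 80% power. The article does not support that in general. It ties 0.40 to stress reduction, which is most naturally read as change, and in change-score SDs power is about 86% at any correlation. A shortfall needs both the raw-score reading and a ρ below about 0.41, and the article settles neither.

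A reader might also take 15 to 35% as a property of this trial. It holds only for an assumed ρ of 0.7 to 0.3 with complete data. Over ρ of 0.8 to 0.2 it would be 10 to 40%, and attrition lowers the gain at T2.

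Finally, the covariate list is open-ended, and a fuller plan may say more. But the article assigns those covariates to a secondary analysis and states the primary model's terms outright. What it fixes for the primary comparison therefore leaves out the T0 score.

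**Conclusion.** The point holds as an efficiency weakness in a valid primary analysis. The direction is certain: with complete data, baseline adjustment lowers the variance for any ρ below 1. The size is not, because it rests on an assumed ρ of 0.3 to 0.7, equal variances, no clustering and, for the T2 figures with attrition, an exchangeable working correlation. On those terms the reduction is 15 to 35% with complete data and about 13 to 30% at T2 with 20% attrition.

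The consequence for power is conditional. In raw-score SDs with ρ below about 0.41, the planned analysis has under 80% power with 116 completers per group, and the adjusted one keeps about 86% or more. In change-score SDs the planned analysis already exceeds its target. Adjustment makes the raw-score case safe against a correlation that the article does not give.

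**What to change.** For each outcome measured at T0, make the primary model a GEE on T1 and T2 with group, time, group × time and the T0 score of that outcome as covariate. Report the adjusted group difference at each of T1 and T2.

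A model over T0, T1 and T2 with a common T0 mean (no group main effect) is an acceptable alternative only with a non-independence working correlation, such as exchangeable or unstructured. Under independence it can lose precision, as shown above.

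State this before outcome data are seen by group, so that the choice to adjust cannot be a response to an observed imbalance. It would also help to say which SD standardises the 0.40.

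The cost is one line of analysis wording and about one degree of freedom. No new data are needed.
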